## Abstract

**Trial registration:**

ClinicalTrials.gov NCT05669378

## Introduction

Active play (AP) in early childhood is an essential part of development [1–5]. This type of play has been positively associated with executive function, social interactions, academic achievement, cognition, language development, mental health, and physical literacy development in early childhood [6–12]. As 56% of Canadian children younger than five years are in early childhood education and care (ECEC), it is an important avenue for increasing AP in early childhood [13]. Evidence that children in this age group have insufficient motor skill proficiency and do not participate in sufficient physical activity while attending ECEC is concerning [14–16]. Early childhood is important for the development of foundational skills and habits that support physical activity participation throughout childhood and into adolescence and adulthood [11,17,18].

In 2017, the Government of British Columbia (BC) recognized the importance of both AP and the ECEC setting to children’s health and development by enacting a mandatory AP standard for licensed ECEC facilities [19–21]. The standard, officially titled ‘The Director of Licencing Standard of Practice - AP’, mandated: the amount of time spent each day in outdoor active play, written screen-time and AP policies, screen time and time spent sitting limits, implementation of facilitated and unfacilitated physical activities and the incorporation of fundamental movement skills (FMS) into routines [19–21]. As part of the rollout strategy, a capacity building intervention, Appetite to Play (https://appetitetoplay.com/), was launched to advance the knowledge and ability of early years providers to implement the AP standard [22–24]. Appetite to Play is a capacity-building approach incorporating a suite of evidence-informed implementation strategies aimed at enhancing the adoption of the AP standard and recommended practices for promoting healthy eating and AP in early years settings [22,23,25]. These are presented in detail elsewhere but include training (community-based and virtual workshops and asynchronous e-learning), resources (e.g., audit and planning tools, an activity and recipe bank, let’s make videos, etc.), community of practice, marketing and communications, and central technical support [22,23]. Scale-up was fully funded during the first 18 months after the release of the AP Standard and the training was provided in-person and online free of charge. Since February 2019, a nominal fee ($14–19) was charged for the training, and content delivery shifted to a primarily online model [19].

Research on Appetite to Play and the impact of the AP standard have demonstrated an increase in the knowledge, confidence and intention of educators to promote AP and healthy eating, and an increase in FMS practices [22,23,26]. Survey research demonstrated improved centre-level policies for AP and increased provision of daily AP and outdoor time, as well as a reduction in screen time [20]. However, following the withdrawal of the funding for Appetite to Play in 2019, survey research has indicated a return to pre-implementation of the AP Standard levels of policies and practices [19]. To date, research on the impact of Appetite to Play and the AP standard has focused on impact at the level of the early childhood educators and managers, and at the policy level of ECEC centres, but has not yet examined child-level outcomes, nor the interaction between managers and educators practices and child-level outcomes. To continue adherence to the standard and sustained use of resources, our research team developed an enhanced intervention called Appetite to Play Plus (ATP+). This intervention builds on the knowledge presented in the original Appetite to Play workshop. ATP+ enhances professional development (training) for ECEC managers and staff supports the application of facility level implementation strategies focused on integrating AP and FMS into scheduling, curriculum planning and creating a supportive environment for AP in ECEC [25]. This paper describes our plan to assess the efficacy of the ATP+ intervention in the context of a randomised control trial (RCT).

### Study aim and hypothesis

The purpose of this research is to investigate whether the enhanced training and resources to support the use/application of facility-level implementation strategies: 1) increases adherence to the BC Directors of Licensing Standard of Practice for AP, and 2) improves 2.5-5.9-year-old children’s FMS. It is hypothesized that centres randomised to the ATP+ intervention will, in comparison to those assigned to the waitlist control group, have greater adherence to the AP standard (time spent in and number of AP, FMS, and outdoor activities), and consequently children attending intervention centres will have greater improvements in their FMS scores over the intervention period. Secondary outcomes will include change in characteristics of providers (skills, self-efficacy, commitment to change), organizational processes (actions to prioritize AP and FMS), and in the environment. It is hypothesised that changes in the secondary outcomes will be higher in centres exposed to the ATP+ intervention as compared to those assigned to the waitlist control group.

## Methods and materials

### Study design

We will recruit 52 ECEC centres to participate in the RCT between 2023 and 2025 from the Metro Vancouver and Greater Victoria regions of BC, Canada. Recruitment began 10/10/2023, with our first data collection 08/11/2023. We anticipate recruitment will finish 15/05/2025. Data collection is anticipated to be completed 30/09/2025 and our results compiled by 01/03/2026. Centres will be recruited through an initial mail invitation and follow-up phone calls. Upon informed consent of centres meeting inclusion criteria, half will be randomised to receive the intervention immediately while the other half will receive the intervention three months post randomization and act as a standard of care waitlist control group. The experimental group will receive the ATP+ intervention, a capacity-building professional development opportunity designed to support ECEC providers in implementing the best practices for AP. The standard of care waitlist control group has access to publicly available Appetite to Play materials during the three-month waitlist period. The SPIRIT Schedule of enrolment, intervention and assessments is outlined in Fig 1, as well a visual of the study flowchart is presented in Figure 2.

**Fig 1 pone.0329276.g001:**
[figure not shown]
SPIRIT schedule of enrolment, interventions and assessments.

**Fig 2 pone.0329276.g002:**
[figure not shown]
Study Flow Chart.

The study is registered at ClinicalTrials.gov (trial ID - NCT05669378), and received ethical approval from the University of BC Behavioural Research Ethics Board (H18-01434).

### Study participants

Inclusion criteria for the ECEC centres are that they are located in the Metro Vancouver or Greater Victoria areas, provide care to at least ten children between the ages of 2.5 to 5.9 years, are licensed for group ECEC/multi-age facility by the local health authority, and provide care to children for more than four hours a day, five days per week. Family ECEC or in-home centres are ineligible to participate. As the ATP+ program requires that managers and educators work together to support AP, at least one manager and two educators who directly care for children that are 2.5 to 5.9 years of age must be willing to try out the ATP+ program and participate in its evaluation. If centres meet the inclusion criteria, the managers and educators must also meet additional inclusion criteria. Managers and educators at the centres must work full time (at least three full days per week), be 19 years or older, and hold Early Childhood Educator certifications. Managers and educators must also be fluent in English, both orally and in writing. Exclusion criteria for educators include if the individual is deemed to be completing administrative assistant duties only. Children at the centres will only be included in data collection specific to gross motor skills if their parents have voluntarily agreed for them to participate in the study and meet the aforementioned age criteria. A minimum of five parents of eligible children from one facility must consent for data collection to occur at such centre.

### Recruitment and consent

Recruitment of the ECEC centres will be conducted by research teams at the Universities of BC and Victoria from October 2023 to May 2025. Waves of letters and emails will be sent out to centres throughout the geographical regions stated in the inclusion criteria. Sending these initial letters and emails in waves, where 20–30 centres are invited simultaneously, allows for more efficient call backs to take place to understand if the centres are interested in participating and for scheduling the baseline data collection. Once centres have been deemed eligible to participate, paper and digital consent forms will be provided to participants. Specifically, managers and staff will receive printed consent forms, while parents/guardians will receive consent forms either on paper or online via REDCap hosted at BC Children's Hospital Research Institute (BCCHRI). Children whose parents have previously consented to participate in the study will also be provided the opportunity to provide verbal assent to participate in the gross motor skill activities on the day. Participation in the study is completely voluntary, and a participant may withdraw at any time without any consequences or any explanation. If a withdrawal does occur, the participant is able to choose to allow the team to retain their data collected to date or not. If the participant chooses to have their data destroyed, any analysis that migh have been conducted up to that point would remain intact due to the anonymous nature of the data.

### Data collection

All study outcomes will be collected at baseline and at follow-up, approximately three months later. This will be post-intervention for the experimental group and prior to the intervention for the waitlist control group.

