### Primary outcomes

***Change in AP and FMS practices***: Child engagement in AP and FMS activities (i.e., time spent in AP, time spent in FMS, number of FMS activities, time spent outdoors, number of outdoor sessions, and an index on the number of best practices facility adheres to) will be measured with field observation and self-report. For field observations, we will use a modified version of the Environment and Policy Assessment and Observation (EPAO) tool [27], which captures type of AP and FMS (locomotor, agility, and/or object/control) activity, duration, location (indoor or outdoor), and intensity of movement. The field observations will initially be completed independently by two trained members of the research team and involve one observer once high intra-observer consistency is obtained. The observations will take place for eight hours of the ECEC centre’s operational times (8:30am-4:30 pm), to capture the activities when most children are present at the facility. The self-report evaluation will be based on questions from the Early Years Survey and the EPAO as a Self-Report instrument (EPAO-SR), adapted to specifically assess the practices targeted by the AP standards in BC, such as providing a minimum of 60 minutes outdoor AP time per day, at least 120 minutes of AP per day, and the use of both facilitated and unfacilitated AP activities that cover FMS [27].

***Change in FMS***: Child FMS will be assessed with the Test of Gross Motor Development version 3 (TGMD-3), a validated, norm-referenced tool for assessing 13 gross motor skills in both locomotor and object control categories [28]. A modified TGMD-3 protocol is commonly used in early childhood movement skill interventions [29]. In this study, we will evaluate six skills: gallop, hop, horizontal jump, two-hand catch, kick a stationary ball, and overhand throw. A composite score will be computed for locomotor and ball skills with a gross motor composite score computed for the analyses. The TGMD-3 performances will be videoed by the research team and scored at a later date. Two members of the research team will independently score the children on the TGMD-3 criteria and discrepancies will be discussed with a third reviewer.

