### Randomization

A computer-generated (www.sealedenvelope.com) randomization schedule will be used to allocate participants in blocks of two, four, six, or eight participants with a randomization ratio of 1:1. The allocation schedule will be concealed in the randomization module of REDCap and only assigned after informed consent and baseline assessments have been completed. Research team members and participants are blinded to allocation at baseline. They will not enter or modify the allocation schedule, as it will be entirely computer-generated. After randomization, participants and research team members will not be blinded to the allocation conditions because participants will know whether they receive the ATP+ intervention immediately or in 3 months, and team members will be tasked with providing intervention group participants access to the intervention. Allocation assignment will be concealed from the researchers at the analysis stage.

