### Data analysis

A hierarchical mixed effect model incorporating both fixed and random effects at the ECEC and child levels will test the impact of ATP+ on the primary and secondary outcomes, while accounting for the clustering of children, educators, and managers within ECEC centres). Following intention-to-treat principles, several analyses will be conducted with each of the primary and secondary outcomes. The corresponding levels of policy and practice variables will be used as the main independent variables, with child-level demographic variables (age, sex) included as covariates. Missing data patterns will be examined to determine proper imputation techniques to use before or during data analysis (e.g., multivariate normal imputation, chained equations, etc.).

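### If season matters for active-play and outdoor time, a model without calendar time gives standard errors that are too wide, because sequential blocking has already balanced the arms over the year

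*Protocol article*

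**What the plan says.** All points are from the protocol article.

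- **Timing (Data collection):** "All study outcomes will be collected at baseline and at follow-up, approximately three months later".
- **Outcomes (Primary outcomes):** the practice outcomes include "time spent in AP, time spent in FMS, number of FMS activities, time spent outdoors, number of outdoor sessions". They come from field observation and self-report. On the field observation: "The observations will take place for eight hours". The number of observation days per visit is not given.
- **Calendar span (Study design):** "We will recruit 52 ECEC centres to participate in the RCT between 2023 and 2025". First data collection was on 8 November 2023, recruitment is expected to end on 15 May 2025 and data collection on 30 September 2025.
- **Allocation (Randomization):** a schedule is used to "allocate participants in blocks of two, four, six, or eight participants with a randomization ratio of 1:1", and the allocation is "only assigned after informed consent and baseline assessments have been completed". That section speaks of participants, but Study design makes clear that centres are randomised.
- **Model (Data analysis):** a hierarchical mixed model with centre and child effects, "with child-level demographic variables (age, sex) included as covariates". No date, season, recruitment-wave or block term is mentioned.

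**The concern.** Three months is a quarter of the yearly cycle. A centre that enters in autumn is followed up in winter, and one that enters in spring is followed up in summer. Time outdoors and number of outdoor sessions are outcomes for which a seasonal effect is plausible, and its sign over the window depends on the entry date.

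Each centre is allocated after its own baseline, in blocks of at most eight, so the allocation sequence follows calendar time and the arms are close to balanced within any stretch of it. The true sampling variance of the arm difference therefore leaves out most of the seasonal variance. A model without a calendar term does not know this and counts that variance as noise. This is the usual result of balancing on a factor at randomisation and omitting it from the analysis.

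The other terms in the stated model do not cure it. A centre random intercept removes a level common to both visits, not a three-month change that depends on entry date. A common visit effect fails for the same reason. Child age and sex cannot absorb season in centre-level minutes.

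At stake is precision on AP minutes, the outcome that set the sample size, with 26 centres per arm.

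**Working it through.** **The plan's own figures.** With 79 educators in 26 centres per group, the mean cluster size is 79/26 = 3.04 and the design effect is 1 + (3.04 − 1) × 0.03 = 1.061, which agrees with the stated 1.06. The 79 cannot be rebuilt because no SD is given. It corresponds to a standardised effect of about 0.46, that is, a coefficient of variation of about 0.33 for a 15% change. None of this is disputed, and none of it gives a seasonal effect.

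**Inputs from the documents.** 52 centres, 1:1, random blocks of 2, 4, 6 or 8 in order of entry, visits three months apart, entry spread over about 18.5 months.

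**Assumed inputs (not in the documents).** Between-centre SD 20 min, day-to-day SD 25 min, and a 12-month cosine of amplitude A min shared by all centres.

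**Hand check on change scores.** The centre effect cancels. Day-to-day noise contributes 2 × 25² = 1250. The difference of two cosines a quarter cycle apart has amplitude A√2, so its variance over a full year is A². With SE = √(variance × 4/52):

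- season removed: √(1250 × 4/52) = 9.8
- A = 20, season left in: √(1650 × 4/52) = 11.3
- A = 30, season left in: √(2150 × 4/52) = 12.9

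Simulation gives 9.8 with season in the model, and 11.1 and 12.6 without it. The small gap is expected, since 18.5 months is not a whole number of years.

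**Baseline-adjusted analysis.** Simulation with 3000 trials per amplitude, regressing centre-level follow-up on arm and baseline, with and without sine and cosine of follow-up month:

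| A (min) | Model SE, no season term | True SE of that estimate | Model SE, with terms | Too wide by |
|---|---|---|---|---|
| 10 | 8.5 | – | 8.2 | about 3% or less |
| 20 | 9.2 | 8.4 | 8.3 | 9.2/8.4 = 1.10 |
| 30 | 10.3 | 8.7 | 8.3 | 10.3/8.7 = 1.18 |

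At A = 0 the model SE is correct. Without the terms, rejection under the null is 3.1% at A = 20 and 1.9% at A = 30; with them it is 5.1% and 5.3%. Clustering entry into waves gives similar standard errors.

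**The same check by share of variance.** Season's share of follow-up variance is (A²/2)/(20² + 25² + A²/2): 50/1075 = 5%, 200/1225 = 16% and 450/1475 = 31% for A = 10, 20 and 30. A second simulation, set up by share instead of minutes, gives these ratios of model SE to true SE without calendar terms:

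| Season's share of variance | 0% | 5% | 10% | 20% | 30% | 50% |
|---|---|---|---|---|---|---|
| Change score | 1.01 | 1.02 | 1.02 | 1.08 | 1.14 | 1.27 |
| Baseline-adjusted | 1.00 | 1.03 | 1.05 | 1.13 | 1.19 | 1.37 |

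With calendar terms the ratio is 0.99 to 1.01, and bias is about zero throughout. For a change-score effect near 80% power, power without and with the terms is 81% and 84% at a 10% share, 82% and 87% at 20%, and 84% and 91% at 30%. If the 52 centres are allocated without blocking, the ratio at a 30% share is 1.00, so the sequential blocking is what makes the unadjusted SE too wide.

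**The case against.** The strongest reply is that this is a condensed article. The Data analysis section says that age and sex are covariates; it does not say that they are the only ones, and a statistical analysis plan that is not shown could add a calendar term. That stands as a limit: a reader might infer that the investigators decided to ignore season, and the documents do not show that. The point survives as a cheap improvement to the model as stated, because that model does not use the balance that the stated randomisation creates.

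Other objections stand in part:

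- **Size.** No seasonal effect is given. An amplitude of 20 to 30 min is a peak-to-trough swing of 40 to 60 min, beside an outdoor minimum of 60 min a day in the AP standard. That is possible, but nothing in the documents supports it. At 10 min the gain is small.
- **Favourable set-up.** The simulated season is a smooth cosine and the fitted terms have the same shape. The analysis is at centre level and baseline-adjusted, whereas the article specifies a mixed model and does not mention baseline adjustment. The change-score results show that the conclusion does not rest on that adjustment.
- **Mostly the reported SE.** The true SE hardly moves (8.4 to 8.3 at A = 20; 8.7 to 8.3 at A = 30).
- **Inferences.** One observation day per visit is inferred from the eight-hour observation, and the article does not say that visit dates are recorded. Self-report is also used, and the day-to-day noise assumed here does not describe it.

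**Conclusion.** The point holds conditionally. If season explains a material share of the variance in observed AP, FMS-practice and outdoor outcomes, the model as stated reports standard errors that are too wide: by about 3% or less, about 10% and nearly 20% at amplitudes of 10, 20 and 30 min, under the assumed SDs. With no seasonality there is no error.

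Two stronger readings are tempting and should be resisted. One is that season confounds the comparison or raises the false-positive rate: it does not, because the blocking balances it, the estimate is unbiased and the test errs on the conservative side. The other is that the standard errors are certainly too wide: that needs a seasonal effect whose size the documents do not give. The calculations cover centre-level minutes and do not bear on the TGMD-3 outcome. This is a moderate loss of precision, not a threat to validity.

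**What to change.** Prespecify, in the analysis plan and before unblinded analysis, sine and cosine terms (12-month period) of the follow-up visit date in the model for each observed AP, FMS-practice and outdoor outcome. The self-reported versions can be handled in the same way, optionally. With visits three months apart, the same two terms also cover the baseline season.

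Prefer these to a four-level season factor, which recovers less. Under the assumptions above, the factor gave no gain in power at A = 10 (81% with or without it; SE 8.4 against 8.5), and at A = 30 it reached 77% power against 82% for the sine and cosine terms.

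The cost is two degrees of freedom and one sentence in the plan. The only data needed are visit dates, so the plan should confirm that these are kept. If season turns out not to matter, almost nothing is lost; adding the terms after seeing the results would look data-driven.

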### Primary outcomes

***Change in AP and FMS practices***: Child engagement in AP and FMS activities (i.e., time spent in AP, time spent in FMS, number of FMS activities, time spent outdoors, number of outdoor sessions, and an index on the number of best practices facility adheres to) will be measured with field observation and self-report. For field observations, we will use a modified version of the Environment and Policy Assessment and Observation (EPAO) tool [27], which captures type of AP and FMS (locomotor, agility, and/or object/control) activity, duration, location (indoor or outdoor), and intensity of movement. The field observations will initially be completed independently by two trained members of the research team and involve one observer once high intra-observer consistency is obtained. The observations will take place for eight hours of the ECEC centre’s operational times (8:30am-4:30 pm), to capture the activities when most children are present at the facility. The self-report evaluation will be based on questions from the Early Years Survey and the EPAO as a Self-Report instrument (EPAO-SR), adapted to specifically assess the practices targeted by the AP standards in BC, such as providing a minimum of 60 minutes outdoor AP time per day, at least 120 minutes of AP per day, and the use of both facilitated and unfacilitated AP activities that cover FMS [27].

***Change in FMS***: Child FMS will be assessed with the Test of Gross Motor Development version 3 (TGMD-3), a validated, norm-referenced tool for assessing 13 gross motor skills in both locomotor and object control categories [28]. A modified TGMD-3 protocol is commonly used in early childhood movement skill interventions [29]. In this study, we will evaluate six skills: gallop, hop, horizontal jump, two-hand catch, kick a stationary ball, and overhand throw. A composite score will be computed for locomotor and ball skills with a gross motor composite score computed for the analyses. The TGMD-3 performances will be videoed by the research team and scored at a later date. Two members of the research team will independently score the children on the TGMD-3 criteria and discrepancies will be discussed with a third reviewer.

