### Sample size calculation

A sample of 79 educators per group, within 26 ECEC centres would be sufficient to detect a 15% improvement relative to control in AP minutes, given an ICC of 0.03, a design effect of 1.06 and an alpha of 0.05 with 80% power [39].

For child outcomes, a similar calculation was performed to estimate the number of children needed to detect a 0.5 standard deviation increase in FMS outcomes with 80% power and an alpha of 0.05. Assuming a 25% attrition rate and that 5 children participate per site at both time points, 92 children per group are needed, which translates to 36 centres. However, since the requirements for educator outcomes are more stringent, 52 centres will be recruited and randomized, and child-level data will be collected at all 52 centres.

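### As written, the video scorers of the primary child outcome may know arm and visit; the plan should state that they and the third reviewer are masked

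*Protocol article*

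**What the plan says.** The Primary outcomes section makes change in fundamental movement skills, measured with six TGMD-3 skills, a primary outcome. On how the score is produced, it says: "The TGMD-3 performances will be videoed by the research team and scored at a later date". It continues: "Two members of the research team will independently score the children on the TGMD-3 criteria", and "discrepancies will be discussed with a third reviewer". It says nothing about whether the scorers or the third reviewer know the centre's arm or whether a clip is from baseline or follow-up.

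The Randomization section covers blinding at three stages:

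- **Baseline:** "Research team members and participants are blinded to allocation at baseline".
- **After allocation:** "After randomization, participants and research team members will not be blinded to the allocation conditions". Two reasons are given: participants know when they receive the programme, and "team members will be tasked with providing intervention group participants access to the intervention".
- **Analysis:** "Allocation assignment will be concealed from the researchers at the analysis stage".

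Video scoring is not mentioned at any of the three stages.

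**The concern.** The people who score the videos are described as members of the research team, and the research team is the group declared unblinded after allocation. TGMD-3 scoring is a judgement of whether a performance meets criteria, so it is open to expectation. The Data collection section places follow-up after the intervention in one arm and before it in the other. The Study aim and hypothesis section predicts greater improvement in the first of these. A rater who knows both arm and visit therefore knows where improvement is expected.

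Two independent scores and a third opinion reduce random error. They do not remove a leaning that all three people share. Concealing arm labels at analysis does not help either, because by then the scores have been given.

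At stake is whether a difference between arms in a primary outcome can be read as a difference between children rather than between raters. Because performances are recorded and scored later, the design already has most of what masked scoring needs.

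**Working it through.** **1. Setting the sections side by side.**

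| Question | Primary outcomes | Randomization |
|---|---|---|
| Who scores? | Two research team members, then a third reviewer | Research team members are unblinded after allocation; no exception for scorers |
| When? | From video, after the visit | Concealment resumes at the analysis stage |
| Why unblinded? | Not addressed | Participants know their timing; the team gives access to the programme |

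Neither reason for unblinding requires a person scoring a recording to know the arm. Scoring is described as outcome measurement, whereas the Data analysis section describes modelling and imputation. The analysis-stage sentence therefore does not naturally reach scoring.

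**2. The plan's own figure.** The Sample size calculation section aims to "detect a 0.5 standard deviation increase in FMS outcomes with 80% power and an alpha of 0.05" and arrives at 92 children per group. The point does not depend on this figure, but it sets the scale.

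- Unclustered, two-sided: n = 2(1.96 + 0.842)² / 0.5² = 62.8 per group.
- Design effect with 5 per site and ICC 0.03: 1 + (5 − 1)(0.03) = 1.12.
- With 25% attrition: 62.8 × 1.12 / 0.75 = 93.8. An ICC of 0.025 gives 92.1.

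The stated 92 is reproduced to within 2.

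**3. What kind of leniency matters.** The outcome is change. If L is the mean leniency in an arm at a visit, the bias in the contrast of change scores is

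b = (L_int,follow-up − L_int,baseline) − (L_ctl,follow-up − L_ctl,baseline).

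Leniency that is equal at both visits within an arm cancels, and so does leniency that is equal in both arms at a visit. Only an arm-by-visit difference remains.

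**4. Illustration of size.** Inputs from the documents: 52 centres allocated 1:1, hence 26 per arm; 5 children per site; 25% attrition; alpha 0.05. Assumptions:

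- The test is two-sided.
- b is 0.1 or 0.2 SD of the analysed change. The documents give no figure for rater bias.
- The ICC is 0.03, which the plan states for educators only.
- Children per centre lie between 5 and 5 × 0.75 = 3.75. The plan's 5 may already be completers, so 3.75 is the cautious end.

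Formulas: n_eff = 26m / [1 + (m − 1)(0.03)]; SE = √(2 / n_eff); δ = b / SE; type I error = Φ(−1.96 + δ) + Φ(−1.96 − δ).

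- m = 3.75: n_eff = 97.5 / 1.0825 = 90.1, SE = 0.149.
- m = 5: n_eff = 130 / 1.12 = 116.1, SE = 0.131.

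| b (SD) | Share of 0.5 SD | δ, m = 3.75 | Type I error | δ, m = 5 | Type I error |
|---|---|---|---|---|---|
| 0 | 0% | 0 | 0.05 | 0 | 0.05 |
| 0.1 | 20% | 0.67 | 0.10 | 0.76 | 0.12 |
| 0.2 | 40% | 1.34 | 0.27 | 1.52 | 0.33 |

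With m = 5 and an ICC of 0.10 instead, the last column becomes 0.105 and 0.276. With b = 0.05 SD, m = 5 and ICC 0.03, it is 0.067.

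**The case against.** **The text may not mean that scorers are unmasked.** Scoring is deferred, and allocation is concealed from researchers at the analysis stage, so a generous reader could count video scoring as part of that stage. The reason given for unblinding need not apply to every scorer. The Data confidentiality and anonymity section also promises data without participant or centre names, files stored under identification numbers, and a procedural manual. What stands is that coded files are partly in place and that some ambiguity remains. But an identification number does not mask arm or visit, and the plan does address blinding, placing team members on the unblinded side without exception. If masked scoring is intended, one sentence would settle it.

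**Bias is not shown.** A reader might infer that the child outcome will be biased towards the intervention. The documents do not support that: they show that the opportunity exists, with no evidence of its occurrence, size or direction. Independent scoring, a third reviewer and masked analysis are partial safeguards.

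**The damage could be undone.** A reader might also infer that nothing could correct the scores afterwards. If the recordings are kept, masked re-scoring could replace them.

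**Staffing is unknown.** It is tempting to say that the two university teams could exchange videos, or that no rater should score a centre they visited. The Recruitment and consent section says only that both universities recruit. It does not say that both score, and no team size is given. This objection stands, so separation of roles can only be asked for where staffing allows.

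**Conclusion.** The point holds as a risk that the written plan leaves open: scorers of a primary outcome, and the third reviewer, may know arm and visit, and nothing stated prevents it. This is a low-cost improvement to the design. It does not show that the trial is biased, and it changes no sample size, power or alpha.

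The type I error figures of about 0.10 to 0.12 and 0.27 to 0.33 show how sensitive the comparison would be. They are not estimates for this trial. They rest on an assumed net arm-by-visit leniency of 0.1 or 0.2 SD in change and on an ICC borrowed from educators. If leniency does not differ by arm and visit together, the error stays at 0.05.

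**What to change.** Add a statement to the Primary outcomes section, matched in the Randomization section and the procedural manual, that the TGMD-3 scorers and the third reviewer are masked to arm and visit. In practice:

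- give each clip a code that carries no information on centre, arm or visit;
- present baseline and follow-up clips in random order;
- where existing staffing allows, use scorers who neither provide access to the programme nor made that centre's follow-up visit;
- re-score under masking any retained videos that were already scored unmasked.

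The cost is recoding and shuffling files, some limits on scheduling raters, and rater time for any re-scoring. Masking will reduce the bias but may not remove it entirely, since the footage itself may reveal the centre or the visit.
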